### Statistical analyses and sample size and power calculations

For this study, 645 participants will be randomized at baseline to test the main effects of smoking and alcohol interventions for the primary smoking outcome (cotinine-verified 7-day smoking abstinence at week 52 follow-up) and alcohol outcome (breathalyzer-verified continuous alcohol abstinence for 90 days at week 52 follow-up). The study is powered to test the primary hypotheses using χ^2^ tests and the secondary hypothesis using Fisher’s exact test. Assuming a two-sided χ^2^ test with a type I error rate of 0.025 for each of two primary outcomes, smoking abstinence rates of 18 % in the IntS+A group versus 8 % in the IS group and 4 % in the UC group, a sample size of 215 participants in the IntS+A group and 430 participants in the IS and UC combined group will achieve a power of 80 %. With 645 participants and a type I error rate of 0.025, we have greater than 90 % power for the primary alcohol hypothesis, assuming 90-day alcohol abstinence rates of 32 % vs. 10 % for the IntS+A group versus the IS intervention or UC groups . Assuming a two-sided Fisher’s exact test with a type I error rate of 0.05 for the secondary outcome of smoking abstinence rate of 12 % in the IntS group versus 4 % in the UC group, a sample size of 215 participants per group will achieve a power of 82 %. Our sample size calculation was based on the analysis that classified those lost to follow-up as smokers or drinkers and therefore has accounted for up to a 25 % attrition rate observed in the prior Power to Quit (PTQ) study [32, 33].

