#### Basis for sample size

We based our estimates for the main outcomes on data from our previous PTQ study among homeless smokers, as well as from the available literature [38, 43]. In the PTQ study, 7-day abstinence rates at week 26 were 9.3 % for the MI+NRT condition and 5.1 % for the control group. In another study [43] of alcohol-dependent smokers, our research team reported 7-day abstinence rates at 6 months as 9.1 % and 2.2 % for an intensive smoking intervention (three counseling sessions + NRT) and brief advice, respectively. We therefore projected the smoking abstinence rates as 4 % for the UC condition and 12 % for the IS condition. Our PTQ study also showed that the smoking abstinence rate for those who quit drinking during the study was nearly double that for drinkers, despite not having an alcohol intervention. We conservatively projected the smoking abstinence rate for the IntS+A condition as 18 %. We based the projection for the alcohol abstinence rates on a study [38] in which our research team found 90-day alcohol abstinence rates of 32–43 % at 12 months among alcohol-dependent smokers.

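### The 80 % power for the primary smoking outcome does not follow from the 215-vs-430 test it is attached to, and the IS rate behind it is 8 % in one place and 12 % in two others

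*Protocol article*

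**What the plan says.** All the figures are in two adjoining sections of the protocol article.

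**Statistical analyses and sample size and power calculations**
- Test and error rate: "Assuming a two-sided χ^2^ test with a type I error rate of 0.025 for each of two primary outcomes".
- Planning rates for the primary smoking outcome: "smoking abstinence rates of 18 % in the IntS+A group versus 8 % in the IS group and 4 % in the UC group".
- Contrast and result: "a sample size of 215 participants in the IntS+A group and 430 participants in the IS and UC combined group will achieve a power"; the value given is 80 %.
- Secondary comparison, two-sided Fisher's exact test at 0.05 with 215 per group: "smoking abstinence rate of 12 % in the IntS group versus 4 % in the UC group", power 82 %. The arm label IntS is used nowhere else in the article; the data analysis section shows that this comparison is IS vs UC at week 52.
- Participants lost to follow-up are counted as failures, so all 645 remain in the denominators.

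**Basis for sample size**
- "We therefore projected the smoking abstinence rates as 4 % for the UC condition and 12 % for the IS condition".
- "We conservatively projected the smoking abstinence rate for the IntS+A condition as 18" %.

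**The concern.** There are two faults in the sentence that justifies the sample size for a primary outcome.

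First, one arm has two planning rates for the same endpoint, verified 7-day abstinence at week 52. The primary sentence uses 8 % for IS; the secondary sentence and the basis section use 12 %. A fuller document could not make both correct.

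Second, the stated power looks too low for 215 vs 430 with a difference of 10 or more percentage points.

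At stake is how the result will be read. A null finding judged against a quoted 80 % is read differently from one judged against 92 % or 99 %. The choice of IS rate also decides what the trial can say about adding alcohol treatment to the intensive smoking programme.

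**Working it through.** **Inputs.** Arms of 215; two-sided alpha 0.025, so z = 2.2414; IntS+A 18 %; UC 4 %; IS 8 % (primary power sentence) or 12 % (secondary power sentence and basis section). No reduction for attrition, because losses count as failures.

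**Combined comparator.** IS and UC are equal in size, so the rate is their mean:
- IS 8 %: (8 + 4)/2 = 6 %
- IS 12 %: (12 + 4)/2 = 8 %

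**Formula** (normal approximation to the χ² test):

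power = Φ[(p1 − p2 − z·s0)/s1], where s0 = √{p̄(1 − p̄)(1/n1 + 1/n2)}, s1 = √{p1(1 − p1)/n1 + p2(1 − p2)/n2}, and p̄ is the overall rate.

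**Attempt to reproduce the stated 80 %: 215 vs 430**

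*Rates as the primary sentence gives them, 18 % vs 6 %.* p̄ = (215 × 0.18 + 430 × 0.06)/645 = 0.100; s0 = 0.02506; s1 = 0.02860. (0.12 − 2.2414 × 0.02506)/0.02860 = 2.23, so power = **98.7 %**.

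*Rates as the basis section gives them, 18 % vs 8 %.* p̄ = (215 × 0.18 + 430 × 0.08)/645 = 0.1133; s0 = 0.02648; s1 = 0.02929. (0.10 − 2.2414 × 0.02648)/0.02929 = 1.39, so power = **91.7 %**.

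**Does the method matter?** Power for 215 vs 430 at alpha 0.025:

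| Method | 18 % vs 6 % | 18 % vs 8 % |
|---|---|---|
| Pooled variance (above) | 98.7 % | 91.7 % |
| Unpooled variance | 97.5 % | 88.0 % |
| Continuity-corrected | 98.3 % | 89.8 % |
| Exact enumeration of the χ² test | 99.1 % | 92.5 % |
| Fisher's exact test | 98.9 % | 91.2 % |

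A three-group χ² test with 2 degrees of freedom gives 99.2 % with IS at 8 % and 97.8 % with IS at 12 %. The lowest value by any of these methods is 88.0 %.

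**What would give 80 %?** With 18 % vs 8 % and 215 vs 215: p̄ = 0.13; s0 = 0.03244; s1 = 0.03208; (0.10 − 2.2414 × 0.03244)/0.03208 = 0.85, so power = 80.3 % (81.1 % by exact enumeration). The sample size for 80 % is then 214 per arm.

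**IntS+A vs IS alone at the 12 % rate.** With 18 % vs 12 % and 215 vs 215: p̄ = 0.15; s0 = 0.03444; s1 = 0.03432; (0.06 − 2.2414 × 0.03444)/0.03432 = −0.50, so power = 30.8 %.

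**Other stated figures.** Alcohol, 32 % vs 10 %, 215 vs 430: above 99.9 %, consistent with the stated greater than 90 %. Secondary smoking comparison, 12 % vs 4 %, 215 per arm, alpha 0.05: 82.4 % with continuity correction and 84.5 % by exact Fisher enumeration. The stated 82 % is acceptable.

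**The case against.** The best defence is that nothing is at risk. The section names its contrast, the stated power is below the true power under either IS rate, and 645 participants are more than enough for that test on the plan's own rates. This stands and limits the point to a correction of stated figures. It does not make the 80 % right or settle the IS rate.

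Three stronger readings are tempting, but the documents do not support them.

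- **That the 80 % is known to be a 215-vs-215 calculation.** The match is close, but the article describes no such primary test. Removing 25 % for attrition (161 vs 322, 18 % vs 8 %) gives 82.3 %, or 78.5 % with continuity correction, which lies on either side of 80 %. That would contradict the rule that losses count as failures, so it does not rescue the sentence. It does leave the origin of the figure open.
- **That the trial is underpowered at 31 %.** That figure belongs to IntS+A vs IS alone, which the article never names as a primary test. The sizing sentence sets IntS+A against IS and UC combined.
- **That the 18 % is shown to be optimistic.** The basis section mentions that participants who quit drinking had nearly double the smoking abstinence, but it does not derive 18 % from this. To obtain a lower figure one must assume an exact doubling, a wholly causal link and no other route to benefit. The plan makes none of these assumptions.

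**Conclusion.** The primary smoking power statement is wrong as written. The IS rate is contradictory (8 % against 12 %), and the stated 80 % belongs to neither version of the stated test. Power for 215 vs 430 at two-sided alpha 0.025 is about 99 % with IS at 8 % and about 92 % with IS at 12 %, so the stated figure is roughly 12 to 19 points too low.

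These results rest on the article's own rates, equal-sized IS and UC arms, and losses counted as failures. They do not depend on the choice of approximation: the smallest gap among the methods tried is 8 points.

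That 8 % is the combined rate reported as the IS rate, and that the power was computed for equal groups, are both plausible inferences, not established facts. The sample size is not too small for the contrast named.

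**What to change.** In the power section:

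1. Use one IS planning rate throughout. The 12 % is better supported, since the basis section and the secondary power sentence both use it; the sponsor should confirm it against the original calculation.
2. Replace the label IntS in the secondary power sentence with IS.
3. Restate the power of the 215-vs-430 test with all its inputs: rates by arm, combined comparator rate, alpha and method. With IS 12 % and UC 4 % (combined 8 %) this is about 92 %.
4. If IntS+A vs IS alone is to be interpreted, add that its power at 18 % vs 12 % is about 31 % at alpha 0.025.

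N, the primary test and the stated secondary 82 % stay as they are. The cost is a few lines of text. The pooled figure becomes more favourable; the figure in item 4, if given, is unfavourable but tells readers what that comparison can show.

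### The stated 80 % power for the primary smoking test does not follow from its own inputs, which give about 99 % (about 92–93 % with the 12 % IS rate used elsewhere); the IS rate and the primary comparison need to be reconciled

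*Protocol article*

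**What the plan says.** The section on statistical analyses, sample size and power of the protocol article gives every input for the primary smoking test in one sentence:

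- Test: "Assuming a two-sided χ^2^ test".
- Error rate: "type I error rate of 0.025 for each of two primary outcomes".
- Rate in the integrated arm: "smoking abstinence rates of 18 % in the IntS+A group".
- Rates in the other two arms: "versus 8 % in the IS group and 4 % in the UC group".
- Sizes and result: "a sample size of 215 participants in the IntS+A group and 430 participants in the IS and UC combined group will achieve a power"; the figure given is 80 %.

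The same paragraph sizes the secondary IS vs UC test on a different IS rate: "smoking abstinence rate of 12 % in the IntS group versus 4 % in the UC group", by Fisher's exact test at 0.05 with 215 per group, for a stated power of 82 %. The subsection Basis for sample size agrees with that second rate: "We therefore projected the smoking abstinence rates as 4 % for the UC condition and 12 % for the IS condition".

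On attrition, the paragraph says: "Our sample size calculation was based on the analysis that classified those lost to follow-up as smokers or drinkers". It adds that this covers up to 25 % attrition. The subsection Analyses for primary hypotheses repeats that losses are treatment failures. It names the chi-square test but does not say which arms are compared, so for smoking the combined comparator is set out only in the power sentence.

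**The concern.** IntS+A at 18 % against a combined comparator of 6 % (the mean of 8 % and 4 % in equal arms) is a threefold ratio with 645 participants. A power of only 80 % looks far too low for that difference. Either the result or one of the inputs must be wrong, and the IS rate is itself given as both 8 % and 12 %.

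Two things are at stake. The first is the accuracy of the power claim for a primary outcome. The second is whether readers can tell which comparison is primary. The sentence with the wrong figure is also the one that defines the pooled smoking comparison, and the candidate comparisons have very different power.

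**Working it through.** **Inputs** (all from the protocol article): two-sided α = 0.025, so z = 2.2414; 215 per arm; IntS+A 18 %; UC 4 %; IS 8 % (power sentence) or 12 % (Basis for sample size, and the secondary calculation). With equal arms the combined comparator rate is (8 + 4)/2 = 6 % or (12 + 4)/2 = 8 %.

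**Formula.** Power = Φ{(|p1 − p2| − z·s0)/s1}, where s0 = √[p̄(1 − p̄)(1/n1 + 1/n2)], s1 = √[p1(1 − p1)/n1 + p2(1 − p2)/n2], and p̄ is the pooled rate.

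**1. The sentence as written: 215 vs 430, 18 % vs 6 %.** p̄ = 0.100, s0 = 0.02506, s1 = 0.02860. (0.12 − 2.2414 × 0.02506)/0.02860 = 2.23, so power is **98.7 %**. Exact enumeration of the chi-square test gives 99.1 %, as does simulation with separate IS and UC counts. The stated 80 % is not reproduced.

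**2. IS at 12 %: 215 vs 430, 18 % vs 8 %.** p̄ = 0.1133, s0 = 0.02648, s1 = 0.02929. (0.10 − 2.2414 × 0.02648)/0.02929 = 1.39, so power is **91.7 %** (exact 92.5 %, simulation 92.6 %).

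**3. Other computing choices at full n, α = 0.025:**

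| Method | 18 % vs 6 % | 18 % vs 8 % |
|---|---|---|
| Unpooled variance | 97.5 % | 88.0 % |
| Continuity-corrected formula | 98.3 % | 89.8 % |
| Fisher's exact | 98.9 % | 91.2 % |
| Three-arm chi-square, 2 df (rates 18/8/4 or 18/12/4) | 99.2 % | 97.8 % |

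None is near 80 %.

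**4. Attrition.** Cutting n by 25 % (161 vs 322) gives 95.2 % with IS at 8 % and 82.3 % with IS at 12 %. Multiplying all rates by 0.75 instead gives 94.6 % and 81.0 %. Only the 12 % versions come near 80 %. A cut in n contradicts counting losses as failures. The secondary calculation also argues against both adjustments. At the full 215 per group with 12 % vs 4 %, the continuity-corrected formula gives 82.4 % and exact Fisher 84.5 %, in line with the stated 82 %. At 161 per group exact Fisher gives 71 %, and with rates of 9 % vs 3 % it gives 70 %.

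**5. What does give 80 %.** 215 vs 215 at 18 % vs 8 %: p̄ = 0.13, s0 = 0.03244, s1 = 0.03208. (0.10 − 2.2414 × 0.03244)/0.03208 = 0.85, so power is **80.3 %**, and 214 per group are needed for 80 %. With IS at 12 %, the same equal-size comparison (18 % vs 12 %) has s0 = 0.03444 and s1 = 0.03432. (0.06 − 2.2414 × 0.03444)/0.03432 = −0.50, so power is **30.8 %**.

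**6. Detectable rate.** Solving the formula for 80 % power at 215 vs 430 gives an IntS+A rate of 13.4 % (combined comparator 6 %) or 16.2 % (combined comparator 8 %).

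**The case against.** **The origin of the 80 % is not established.** This stands. The equal-size calculation fits best, but 8 % is also exactly the mean of 12 % and 4 %. The figure labelled as the IS rate may be the combined comparator rate, mislabelled, with equal group sizes entered by mistake. The declared comparator would then be right. Rates of 18, 12 and 4 % deflated by 0.75 reach 81.0 % on the declared comparison as well, although the secondary calculation does not follow that rule. A reader might infer that the trial was really powered for IntS+A vs IS and that the declared comparator is wrong. The document does not show that.

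**The 99 % rests on the less supported rate.** This also stands. The 12 % rate appears twice and is the reasoned projection; the 8 % appears once. Printing 99 % before the rate is settled could fix the wrong input. Neither rate gives 80 %, however.

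**The sample size does not depend on this figure alone.** Agreed. A reader might infer that 645 is larger than needed, since the pooled test reaches 80 % with far fewer. But the secondary IS vs UC test needs about 195 per arm for 80 % by exact Fisher, that is 3 × 195 = 585 in total, and has 84.5 % at 215. The arm size has its own support.

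**80 % could be meant as a floor.** This does not stand. The sentence states a value, whereas the next one, on alcohol, is worded as exceeding 90 %. The authors marked a lower bound where they meant one.

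**Conclusion.** The stated 80 % is wrong for the comparison it is attached to. With the sentence's own inputs the power is about 99 %; with IS at 12 % it is about 92–93 %. This rests on the stated two-sided 0.025 level, equal arms of 215, and losses counted as failures at full n, all of which the article gives.

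On the declared comparison the error understates power. It does not invalidate the test, its error rate or the sample size, and the pooled test is not underpowered. The practical harm is that the IS rate and, through it, the intended comparison are left uncertain. If a 215 vs 215 comparison of IntS+A with IS was meant, power is about 80 % at 18 % vs 8 % but only about 31 % at 18 % vs 12 %. That low figure is conditional on a comparison the article does not declare, so it should not be read as a finding that the trial lacks power.

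**What to change.** 1. Settle the IS abstinence rate, 8 % or 12 %, and use it in the power sentence, the secondary calculation and Basis for sample size. If 8 % is the combined comparator rate, label it so.
2. Confirm that the primary smoking comparison is IntS+A against IS and UC combined, and say so in Analyses for primary hypotheses.
3. Restate the power for 215 vs 430 at 0.025: about 99 % with IS at 8 %, or about 92–93 % with IS at 12 %. Alternatively give the IntS+A rate detectable with 80 % power: about 13.4 % or 16.2 %.
4. If a 215 vs 215 comparison was meant, name it, give its two rates, correct the group sizes in the sentence and state its power.

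Keep 645. If the pooled comparison is confirmed, the cost is one recalculation and a few corrected sentences, with no added participants and no change in conduct.

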In our recently completed Power to Quit (PTQ) study (*N* = 430) [32, 33] targeting homeless smokers, we found cotinine-verified 7-day quit rates to be 9.3 % for motivational interviewing (MI) vs. 5.6 % for the control group at 26 weeks. These quit rates are low when compared with those in the general population, demonstrating the challenge for a smoking intervention in homeless populations. A variety of factors may have contributed to low quit rates in the study, including (1) high level of nicotine dependence as indicated by mean 20 cigarettes per day and 87 % of the participants smoking their first cigarette within 30 minutes of awakening, (2) high rates of substance abuse and psychiatric comorbidities [18, 19], (3) competing daily social needs and (4) need for more cognitive behavioral strategies instead of MI, given the high baseline motivation to quit (9+ on a 1–10 scale). The low quit rates revealed in studies of alcohol-dependent and homeless smokers, along with positive outcomes in studies of combined NRT, suggest that a more intensive intervention ought to be considered. The primary aim of the present study is therefore to evaluate the effects of an intensive smoking intervention that integrates alcohol abuse treatment and smoking cessation in a homeless population. We will use a three-group randomized design to test the study hypotheses in a community-based setting. The three study conditions are (1) integrated intensive smoking intervention using cognitive behavioral therapy (CBT) plus alcohol intervention (IntS+A), (2) an intensive smoking (IS) intervention using CBT or (3) usual care (UC; brief smoking cessation and brief alcohol counseling, both based on U.S. Public Health Service [USPHS] guidelines) [34, 35]. In addition, all participants will receive a 12-week treatment with a combination of nicotine patch plus gum or lozenge.

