### Intervention components

#### Integrated intensive smoking intervention using cognitive behavioral therapy plus alcohol intervention

Participants in the IntS+A group will receive separate alcohol and smoking counseling during each session. Each session will be broken down into two 30-minute segments of distinct alcohol counseling and smoking intervention. Participants will receive weekly counseling for the first 3 months, followed by monthly group sessions for the next 3 months. After the initial session, the counselor will allow the participant to decide whether to address alcohol or smoking first, and each subsequent session will alternate which topic begins the session. The content covered in the smoking module in the IntS+A condition is identical to that in the IS condition. The CBT model employed to address both smoking and alcohol follows the antecedent–behavior–consequences) model and places equal weight on identifying and changing thought patterns as behavior modification. Counselors will encourage participants to identify their antecedent thoughts and situational factors (i.e., triggers and cues) contributing to their smoking and alcohol use and to examine the consequences of their use. The alcohol counseling will be distinct from smoking counseling, and in it similarities between quitting smoking and stopping alcohol and drug use will not be emphasized. This is based on findings from a study [39] in which researchers reported that emphasizing these similarities led to worse alcohol outcomes compared with concurrent treatment that did not emphasize the similarities. The alcohol intervention manual is based on the National Institute on Drug Abuse manual for CBT for drug abuse [38, 39]. The treatment manuals and participant handbooks were developed using both the alcohol treatment protocol used by Cooney and colleagues [38] and a CBT approach [38, 40]. Both manuals were modified to address the needs of this trial. The key alcohol interventions will include self-monitoring of triggers, cravings and urges; and functional analysis of drinking behavior (i.e., antecedents, behavior and consequences).

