#### Analyses for primary hypotheses

The primary analysis will be based on an intention-to-treat analysis; that is, participants will be analyzed regarding the treatment to which they were randomized. The intervention effects for the primary outcomes of week 52 biochemically verified 7-day abstinence from cigarette smoking and week 52 ninety-day abstinence from alcohol consumption will be tested using χ^2^ tests. Any participants lost to follow-up will be classified as treatment failures (i.e., smoker or drinker). Bonferroni procedures will be used to control for experiment-wise type I error rate. Abstinence rates and corresponding 95 % confidence intervals will be estimated and summarized using appropriate tabular and graphical methods.

In supportive analyses, we will examine baseline variables, including demographics (age, sex, income and education), nicotine dependence, withdrawal symptoms, motivation and confidence, self-efficacy, social support, perceived stress and depressive symptoms, in terms of their relationship to study outcomes. Analyses accounting for these measures will be conducted using multiple logistic regression including intervention groups as controlled factors. Thus, we will be able to assess whether the main conclusions from the primary analysis are robust for the inclusion of these baseline variables. Fisher’s exact test will be used to compare the biochemically verified 7-day smoking abstinence rates at week 52 follow-up between the IS and UC participants. Supportive analysis will be conducted using multiple logistic regression including the intervention group as a predictor, adjusting baseline covariates to assess whether the result from secondary analysis is robust for the inclusion of baseline covariates.

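### For smoking, the primary test sets IntS+A against IS and UC combined and no IntS+A vs IS test is named, so a positive result cannot by itself be credited to integrating alcohol treatment

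*Protocol article*

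**What the plan says.** All references are to the protocol article.

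- **Primary smoking contrast.** The section on statistical analyses, sample size and power compares 215 IntS+A participants with "430 participants in the IS and UC combined group". It uses a two-sided χ² test with a "type I error rate of 0.025 for each of two primary outcomes" and claims 80 % power. The rates in that sentence are "18 % in the IntS+A group versus 8 % in the IS group and 4 % in the UC group".
- **Basis for the rates.** Under Basis for sample size the IS rate differs: "We therefore projected the smoking abstinence rates as 4 % for the UC condition and 12 % for the IS condition". IntS+A is projected at 18 %.
- **Other smoking tests.** Analyses for primary hypotheses says only that the primary outcomes will be tested with χ² tests. The one pairwise smoking test it names uses Fisher's exact test to "compare the biochemically verified 7-day smoking abstinence rates at week 52 follow-up between the IS and UC participants".
- **Arms.** On IntS+A the article states: "The content covered in the smoking module in the IntS+A condition is identical to that in the IS condition". UC receives a single session of about 20 minutes. IS participants also receive the brief alcohol counseling given to UC.
- **Purpose.** The Abstract and the Discussion both describe a trial of the efficacy of integrating alcohol treatment with smoking cessation. The Background words the primary aim more broadly: to "evaluate the effects of an intensive smoking intervention that integrates alcohol abuse treatment and smoking cessation in a homeless population".

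**The concern.** IntS+A and IS have the same smoking content, so the comparison between them shows what the alcohol component adds for smoking. UC differs from IntS+A in two ways: it has no alcohol CBT and no smoking CBT. Making UC half of the comparator brings the effect of smoking CBT over brief advice into the test. The plan itself expects that effect to be material, because it powers a separate IS vs UC test on it.

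Pooling is defensible for the alcohol outcome, where IS and UC receive the same brief alcohol counseling. The problem is specific to smoking.

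At stake is the reading of a positive primary result. It could be reported as evidence for integration when smoking CBT alone produced it, and no specified smoking test would separate the two explanations.

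**Working it through.** **Inputs.** Arms of 215/215/215; two-sided α = 0.025 (z = 2.2414); IntS+A 18 %; UC 4 %; IS 8 % (power statement) or 12 % (Basis for sample size). Losses count as smokers, so n is not reduced.

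**1. What the pooled contrast estimates.** With equal arm sizes,

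p(IntS+A) − ½[p(IS) + p(UC)] = [p(IntS+A) − p(IS)] + ½[p(IS) − p(UC)].

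The first bracket is the integration effect and the second is half of the smoking-CBT effect.
- IS 8 %: 18 − 6 = 12 points, made up of 10 + 2.
- IS 12 %: 18 − 8 = 10 points, made up of 6 + 4.

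**2. The plan's 80 %.** Normal approximation to the χ² test: power = Φ[(d − z·s₀)/s₁], where s₀² = p̄(1 − p̄)(1/n₁ + 1/n₂) and s₁² = p₁(1 − p₁)/n₁ + p₂(1 − p₂)/n₂.

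| Contrast | n | d | s₀ | s₁ | Power (approx.) | Power (exact) |
|---|---|---|---|---|---|---|
| 18 % vs pooled 6 % (IS 8 %) | 215 vs 430 | 0.12 | 0.02506 | 0.02860 | 98.7 % | 99.1 % |
| 18 % vs pooled 8 % (IS 12 %) | 215 vs 430 | 0.10 | 0.02648 | 0.02929 | 91.7 % | 92.6 % |
| 18 % vs IS 8 % | 215 vs 215 | 0.10 | 0.03244 | 0.03208 | 80.3 % | 81.1 % |
| 18 % vs IS 12 % | 215 vs 215 | 0.06 | 0.03444 | 0.03432 | 30.8 % | 30.7 % |

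The exact column enumerates the binomial distributions. In the pooled rows the comparator is the sum of Bin(215, p(IS)) and Bin(215, p(UC)).

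The stated 80 % is not reproduced for 215 vs 430 under either IS rate. It is reproduced for 18 % vs 8 % with 215 per arm, where 80 % power needs 214 per arm.

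**3. Pooled test when integration adds nothing.** Set IntS+A = IS and UC = 4 %; exact enumeration at α = 0.025:
- Both arms 8 %: pooled comparator (8 + 4)/2 = 6 %; rejection probability 10.9 %.
- Both arms 12 %: pooled comparator (12 + 4)/2 = 8 %; rejection probability 28.1 %.

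Almost all of these rejections favour IntS+A. The normal approximation gives 11.0 % and 28.7 %.

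**4. Power for the contrast that isolates integration.** From the last two rows of the table, IntS+A vs IS at 0.025 has about 81 % power if IS is 8 % and about 31 % if IS is 12 %. In the second case 80 % power would need 672 per arm.

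**The case against.** **The aim may be the whole package.** The Background and the design overview allow that reading, and the pooled test is valid for what it compares. This softens the point. It does not remove it, because the Abstract and Discussion make the integration claim. A comparator that is half IS and half UC also isolates neither the package effect (IntS+A vs UC) nor the integration effect (IntS+A vs IS).

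**A pairwise test may have been intended.** The 80 % fits 18 % vs 8 % at 215 per arm, and the power statement lists IS and UC rates separately. Equally, the 8 % could be the mean of 12 % and 4 %. The document does not settle this, so the fix must cover both cases.

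**An IntS+A vs IS estimate is obtainable anyway.** Arm-level abstinence rates with confidence intervals and a supportive logistic model with intervention groups are planned. That is true, but neither is specified as a test of this contrast. The analysis plan is not shown and may add one; the objection here is to the contrast that the article does state.

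Three stronger readings are not supported:
- *Inflated type I error.* With rates of 12/12/4 the pooled null (12 % vs 8 %) is false, so rejecting it is correct. The error lies in the attribution.
- *A much higher misattribution rate.* Setting IntS+A = IS = 18 % gives 58 %, but nothing in the article projects 18 % for IS.
- *IntS+A vs IS is absent for every outcome.* This can be said only for smoking, because the alcohol power statement can be read pairwise.

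**Conclusion.** The point holds for the smoking outcome. As written, a significant primary smoking test cannot on its own support a claim that integrating alcohol treatment helps smokers quit. With no integration effect and UC at 4 %, the test would be significant about 11 % of the time (IS 8 %) or 28 % (IS 12 %), and the result could be wrongly credited to integration. These figures assume 215 per arm, a two-sided α of 0.025 and losses counted as smokers.

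A reader might infer that the integration question is bound to be underpowered. The documents do not support that outright: power for IntS+A vs IS is about 31 % or about 81 %, depending on which of the article's two IS rates applies.

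Even IntS+A vs IS is not a pure test of alcohol content. The design overview gives sessions of 50–60 minutes for IntS+A and 20–30 for IS, so the contrast estimates added alcohol CBT together with added contact time.

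**What to change.** 1. Keep IntS+A vs IS and UC combined as the first smoking contrast, and read it as IntS+A against a mixed comparator.
2. Add IntS+A vs IS for week-52 cotinine-verified abstinence, tested at the same 0.025 only if the first contrast is significant.
3. State that a benefit of integration for smoking is claimed only on the second test. Report its risk difference with a confidence interval whatever the first test shows.
4. Reconcile the projected IS rate (8 % or 12 %), correct the 80 % figure, and state the power of IntS+A vs IS for the rate chosen.
5. If IntS+A vs IS was the intended primary test, correct the combined-group wording in the power statement instead of taking steps 1 and 2.

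The cost is wording and one further 2×2 test. The fixed sequence uses no extra alpha and no participants are added. The downside is that the integration claim may prove low-powered, and the report should state the contact-time caveat.
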